## Abstract

**Background:**

Psychotherapy for Prolonged Grief Disorder (PGD), a condition characterized by an intense and persistent grief response, has received increased attention over the past decades. Evidence-based approaches to prevent PGD are currently scarce, and not always effective. This paper introduces a protocol for a clinical trial exploring the effectiveness of a Meaning Reconstruction psychotherapy approach (MR) assisted with ayahuasca, a traditional indigenous medicine.

**Method:**

The outlined protocol is a three-arm, non-randomized controlled trial focused on reducing normal and pathological grief symptoms, comparing the effectiveness of Ayahuasca-assisted MR therapy (A-MR), MR therapy alone (MR) and No Treatment (NT). At least 69 people who lost a first-degree relative during the prior year, and with a Texas Revised Inventory of Grief score up 39 (TRIG ≥ 40), will participate in the trial. Participants will be allocated to an A-MR (n ≥ 23), MR (n ≥ 23) or NT (n ≥ 23) group. Those from the A-MR and MR therapy groups will undergo a therapeutic process involving 9 sessions of online psychotherapy. In addition, the A-MR condition involves 2 group sessions of ayahuasca. The primary outcomes will be normal and pathological grief severity as measured by the TRIG and Traumatic Grief Inventory Self-Report (TGI-SR), administered at baseline, post-treatment, and 3-month follow up. Measures of quality of life, post-traumatic growth, meaning-made, psychological flexibility, and self-belief consistency will be also included. In addition, subjective effects of ayahuasca and acceptance-avoidance promoting effects will be assessed following ayahuasca administration. Finally, we will analyze the potential mediating effect of meaning-made, psychological flexibility and self-belief consistency in grief symptoms (as measured by the TRIG and TGI).

**Discussion:**

This trial is the first to empirically examinate the potential of psychedelic-assisted psychotherapy for grief, as well as the potential processes of change that may account for it.

**Clinical trial registration:**

https://clinicaltrials.gov, identifier NCT06150859.

## Introduction

1

Grieving the death of a loved one is a nearly universal experience, and one which may be experienced multiple times over the course of a lifetime. Recent studies have shown that, for each death, approximately nine relatives are directly affected (1). The loss of a first-degree family member significantly increases the risk of mortality, disease, and suicide for the mourner (2–6). Although grief is a natural process, and serves a key existential purpose (7), this psychological process can go awry. Over the last century, different theories have explored how grief itself can become complicated or pathological.

Prolonged Grief Disorder (PGD) has been recently incorporated as a diagnosis into the ICD (ICD-11; 8) and the DSM (DSM-5-TR; 9). PGD is characterized by (1) separation distress (i.e. a persistent grief response involving intense longing and preoccupation), (2) intense emotional reactivity (e.g. anger, denial, blame, emotional numbness, meaninglessness, avoidance), and (3) significant functional impairment (10, 11) according to the mourner’s sociocultural context. This reaction should persist to a marked degree for a minimum of 6 months, following the ICD-11 (8), or 12, months following the DSM-5-TR (9).

The inclusion of PGD in the psychiatric diagnostic system is not without controversy. Besides the difficulties of distinguishing normal from prolonged grief, and the arbitrariness involved in categorizing continuous variables such as distress or time (10), it has been argued that the requirement for these diagnoses may lead to people experiencing acute grief not receiving appropriate healthcare (12). On the other hand, people in Western countries are rapidly losing the cultural knowledge, tradition, and rites to cope with the death of a loved one (13). In this social context, imposing a 6-to-12-month wait for receiving evidence-based psychological support can leave bereaved people abandoned in the most vulnerable state, especially for those at moderate or high health risk.

Despite the WHO’s emphasis on the importance of preventive strategies for addressing the global burden of mental health issues (14), and on loneliness as a significant public health issue (15), evidence-based approaches to prevent PGD are still scarce. Moreover, meta-analyses have shown that preventive therapies for PGD are not currently effective (16, 17). Innovation is therefore necessary to provide effective psychotherapeutic and community support to people in the acute period of grief (18).

### Psychedelic-assisted grief therapy

1.1

Psychedelic-assisted psychotherapy (PAP), a therapeutic approach augmenting talking therapy with psychedelic substances, has been recently classified as a potential breakthrough treatment for psychiatric illness (19). PAP is demonstrating promising outcomes in treating a wide range of mental health issues, ranging from depression to post-traumatic stress disorder, suggesting this efficacy may be transdiagnostic (20, 21). Controlled studies to date have been primarily focused on MDMA-assisted therapy for PTSD (22) and psilocybin-assisted therapy for treatment-resistant depression (23), but it has been proposed that psychedelics could also serve as a prophylactic or preventive intervention with the potential to improve quality of life, well-being, creativity, and personal and spiritual growth (24, 25).

Ayahuasca, a traditional indigenous medicine, has been investigated as a potential treatment for treatment-resistant depression (26). Several studies have evidenced that individuals who regularly use ayahuasca in a communal setting exhibit a higher level of general well-being, increased physical activity, and balanced diet than the general population (27–29). While ayahuasca may not cause physical or psychological dependence, and serious adverse effects are uncommon in healthy individuals (30), some users have reported experiencing psychological distress during its acute effects (31). In a global survey involving 10,836 participants, 2.3% reported requiring medical support following ayahuasca use (32). Additionally, there have been a few documented instances where its consumption has been associated with the emergence of psychotic episodes (33). Nevertheless, most adverse effects can be mitigated by conducting a thorough assessment of participants’ health status prior to administration, ensuring the composition and purity of the ayahuasca preparation, administering an appropriate dosage, and avoiding potential drug interactions (30) (see Section Potential Adverse Effects Management).

Despite the promising outcomes reported in the treatment of several mental health issues, no controlled studies have been conducted testing the efficacy of PAP for PGD, nor have any evaluated PAP’s potential in preventing prolonged grief when administered in the early course of bereavement. Previous observational research, however, has suggested that the ceremonial use of ayahuasca has therapeutic value in reducing the severity of grief (34–36). We therefore propose that ayahuasca assisted with an evidence-informed therapeutic approach, the meaning reconstruction model (37, 38), could show greater reduction in grief severity than psychotherapy alone.

The rationale behind this hypothesis is grounded in a wide range of neurobiological and psychological evidence. Ayahuasca is an Amazonian concoction, usually prepared from the *Banisteriopsis caapi* vine and the *Psychotria viridis* shrub, which has been utilized for healing and ritual purposes since pre-Columbian times (39). Regarding the neurobiological evidence, *in vitro*, animal and human studies have demonstrated how harmine, tetrahydroharmine, harmaline (all three present in *B. caapi*) and dimethyltryptamine (present in *P. viridis*) stimulate adult neurogenesis and neuroplasticity, similarly to other serotoninergic psychedelic substances (40–43). A window for neuroplastic changes would appear to open a few hours after administration, lasting from a few days to a month (44). This period has been related to improvement in grief, depressive mood, stress, mindfulness, acceptance, emotion regulation, social behavior, wellbeing, and quality of life (45). Moreover, elevated peripheral Brain-Derived Neurotropic Factor (BDNF) levels have been observed in healthy volunteers and clinically depressed patients two days following the ayahuasca administration, correlating with clinical improvement in those who were diagnosed with major depression (40). Recent studies have shown that psychedelics reopen a critical period to induce metaplasticity, which dynamically regulates the potential for synaptic plasticity (46, 47). This critical period is context-dependent and has been linked to the ability to induce social reward learning, psychological flexibility, cognitive reappraisal and new patterns of behavior (46, 48, 49). In sum, these studies highlight the importance of the post-treatment integration period to maximize the therapeutic effect of psychedelics.

Looking beyond the neurobiological evidence, several studies indicate that the therapeutic effect is experience-dependent (50, 51). Current research points toward specific traits of the psychedelic experience as relevant mediators of the therapeutic outcomes of PAP, such as acceptance-related experiences, the presence of mystical experiences, or the reappraisal of negative emotion (52–55). The altered state of consciousness induced by psychedelics is characterized by high sensitivity to the immediate and previous context, which can help actualize of the person’s belief system with bottom-up information (56). The ayahuasca experience, therefore, could bring new information to the foreground to enrich the therapeutic process, providing an opportunity to transform maladaptive narratives about oneself, other people (including the deceased) or the world (56, 57). The preparatory psychotherapeutic work, moreover, could bring to light potential blockages or resistances, allowing for an appropriate preparation of the patient’s mindset and intention before the administration of ayahuasca. Lastly, psychotherapy following ayahuasca administration (including, but not limited to, psychedelic integration) could likewise help to promote new behavior, in a way that is congruent with reappraised cognitive schemas derived from the assimilation and accommodation of the experience during this critical period.

We posit, in sum, that ayahuasca experiences, when taking place within the framework of an appropriate and effective psychotherapeutic intervention, could enrich the clinical treatment of grief. This would allow for the integration of new information evoked from the psychedelic experience, and for this to result in more adaptive behavior and coping. We also hypothesize this would favor grief adaptation through fostering psychological processes such as meaning reconstruction, experiential acceptance, or cognitive reappraisal during a period of heightened meta-plasticity.

## Study protocol

2

### Study design and hypotheses

2.1

This three-arm, non-randomized controlled trial investigates the efficacy of Ayahuasca-assisted Meaning Reconstruction therapy (A-MR) in decreasing normal and pathological grief symptoms in people who have lost a first-degree relative within the prior 12 months. Participants are sequentially allocated to the following treatment conditions: (1) a control group receiving Meaning Reconstruction therapy (MR), (2) a control group receiving No Treatment (NT), and (3) an experimental group receiving Ayahuasca-assisted Meaning Reconstruction therapy (A-MR).

The objective of this trial is two-fold. First, our aim is to compare the efficacy of A-MR with that of MR and NT by assessing differences in (a) the severity of normal grief symptoms, (b) pathological grief symptoms, (c) quality of life, and (d) posttraumatic growth. Moreover, we are also interested in analyzing how each condition may influence the proposed processes of change: (e) meaning-made (f) psychological flexibility, and (g) self-belief consistency. Additionally, we will explore the participants’ (h) subjective effects of ayahuasca and the (i) acceptance-avoidance promoting effects.

The following hypothesis will be tested:

Hypothesis 1. The experimental group receiving A-MR will show greater improvement in normal and pathological grief symptoms, quality of life, and post-traumatic growth compared to both control groups (MR and NT), at post-treatment and 3 months follow-up. Moreover, MR group will show greater improvement than the NT group, expecting a medium clinical effect size.

Hypothesis 1.1. The experimental group receiving A-MR will show greater improvement in psychological flexibility, meaning-made, and self-believed consistency compared to both control groups (MR and NT), at post-treatment and 3 months follow-up. Furthermore, MR will also show greater improvement than the NT group, expecting a medium clinical effect size.

Hypothesis 2. Reductions in the severity of normal and pathological grief symptoms will be principally related to changes in meaning- made, but also to changes in psychological flexibility and self-belief consistency. Moreover, a stronger relationship between changes in the severity of grief symptoms and meaning-made is expected in the A-MR group.

### Participants

2.2

Participants eligible for this study will be English and Spanish-speaking adults experiencing grief symptoms due to the death of a loved one. Inclusion criteria involve: (1) people aged 18-65; (2) having experienced the loss of a first-degree relative; (3) within the past 12 months; and (4) with a Texas Revised Inventory of Grief score over 39 (TRIG ≥ 40). Exclusion criteria involve: (1) medically and mentally significant health conditions; (2) history of psychotic disorder (Axis I- DSM-IV-TR); (3) pregnant or breastfeeding women; (4) hypertension (SBP > 140 mmHg, DBP > 90 mmHg, HR >100 bpm); (5) substance use disorder, excluding nicotine; (6) alcohol consumption exceeding 40g/day; (7) concurrent psychological or pharmacological treatment for grief. Those who are not eligible will be referred to other mental health professionals specialized in bereavement.

### Procedure

2.3

Participants will be recruited through the newsletter, webpage, and social media accounts of the Beckley Foundation, Beckley Med, MIND Foundation and the International Center for Ethnobotanical Education, Research and Service (ICEERS), all of them European institutions dedicated to psychedelic research and education. Upon receiving the request to participate in the trial, the participant will be prompted to complete a short online questionnaire to screen for inclusion criteria. Those who meet the inclusion criteria will attend a video-call interview with the principal investigator (DG) to learn more about what their participation would entail and to screen whether any exclusion criteria are met. They will also be informed about the need to verify their blood pressure range with a general practitioner to prevent potential ineligibility, given that blood pressure measurement is taken on-site before each ayahuasca session. Then, those who are eligible will provide informed consent. Assessments will be conducted online at baseline (T0), during treatment (T1 and T2), at post-intervention (T3), and at 3-month follow-up (T4) (see **Figure 1**).

**Figure 1 f1:**
[figure not shown]
Flow-chart of the recruitment procedure.

Participants in the A-MR and MR group will undergo a 9-session online psychotherapy process, starting within 2 weeks after the baseline assessment is completed. Only those in the A-MR group will participate in up to two onsite ayahuasca sessions throughout the therapeutic process, preceded by an online preparation session, and followed by a 50-minute MR online integration session during the week after each ayahuasca experience. For ethical reasons, participants in either control group (MR or NT) have the option to participate in two ayahuasca sessions over a single weekend, once follow-up assessment is completed, if their grief symptom severity are still significant (TRIG ≥ 40), proceeded by a preparation session and followed by two integration sessions to process the experience. **Table 1** shows the measures used at each of the time points.

**Table 1 T1:** Enrolment, intervention, and assessment schedule (SPIRIT).

	STUDY PERIOD									
	Enrolment	Baseline	Allocation	Treatment					Post-treatment	Follow-up
TIMEPOINT		(T0)		Phase 1	Ayahuasca (T1)	Phase 2	Ayahuasca (T2)	Phase 3	(T3)	(T4)
ENROLMENT										
Eligibility screen	x									
Informed consent	x									
Allocation			x							
INTERVENTION										
MR				x		x		x		
NT										
A-MR				x	x	x	x	x		
ASSESSMENT										
TRIG	x	x							x	x
TGI-SR		x							x	x
PSGI-SF		x							x	x
WHO-qol-BREF		x							x	x
AAQ-II		x							x	x
ISLES-SF		x							x	x
SCS		x							x	x
5D-ASC					x		x			
APEQ					x		x			
SA									x	

MR, Meaning Reconstruction Therapy; NT, No treatment; A-MR, Ayahuasca-assisted Meaning Reconstruction Therapy; TRIG, Texas- Revised Inventory of Grief; TGI-SR, Traumatic Grief Inventory self-report; PSGI-SF, Post-traumatic Growth Inventory‐Short Form; WHO-qol-BREF, World Health Organization Quality of Life-Brief; AAQ-II, Acceptance and Action Questionnaire II; ISLES-SF, Integration of Stressful Life Experiences Scale Short-Form; SCS, Self-concept clarity Scale; 5D-ASC, Altered State of Consciousness Rating Scale; APEQ, Acceptance/Avoidance-Promoting Experiences Questionnaire Scale; SA, Level of Satisfaction and Adverse Effects

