##### Texas Revised Inventory of Grief (TRIG)

2.5.1.1

This self-report measure quantifies the severity of normal grief (59). In this trial, only one scale (the Present Feelings Scale, PFS) was used to assess the participant’s emotional state. This 13-item scale is scored on a 5-point Likert-type scale (from 1 = ”completely false” to 5 = ”completely true”) ranging from 13 to 65. Scores up to 39 (TRIG ≥ 40; above the 50th percentile), are defined as severe grief (60). The TRIG has been shown to have adequate psychometric properties, with the PFS having a Cronbach’s coefficient alpha value of.90 (61).

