## Discussion

3

This clinical trial is the first to examine the potential of psychedelic-assisted grief therapy and, more specifically, of ayahuasca-assisted meaning reconstruction therapy for the reduction of the severity of grief symptoms. The study also investigates whether the intervention promotes quality of life and post-traumatic growth, while exploring a series of processes of change that may mediate this therapeutic effect. If this intervention proves to be both feasible and effective upon completion of this study, a future clinical trial will be designed with a focus on (a) prioritizing the mechanism(s) of change that will be identified through mediation analyses.

A key limitation of the trial is that the sequential allocation of participants may have a bias influence on the outcomes. Another limitation is a threat to external validity connected to the recruitment process: the self-referral process relies on the social media presence of psychedelic research and education institutions and associations, which may limit the generalizability of the clinical outcomes to the general population. Moreover, the fact that ayahuasca is a plant concoction complicates the determination of which alkaloids and active compounds influence the outcomes. Finally, accepting bereaved people who meet the ICD-11 sixth-month-since-the-loss criterion for PGD disorder (instead of the more conservative 12-month criterion) could blur the distinction between prevention and treatment. Nevertheless, we will also analyze PGD criteria following the ICD-11 as a potential moderator.

Given the lack of grief literacy in the general population, the widespread loneliness in Western society, and lack of mental health support during the early stages of bereavement, it is imperative to improve bereavement support for acute grief (13). The scarcity of evidence-based therapies for the prevention of PGD indicates the urgent need for new interventions to support bereaved people at moderate-to-high risk, according to the four-tier model (116). We anticipate that the outcomes of this trial will significantly contribute to the field of bereavement care, helping to reduce the time needed for the bereaved to receive evidence-based support, and promoting their adaptation. Moving beyond the context of grief and loss, this study will also contribute to advancing our understanding of PAP as way to prevent and reduce the global mental health burden (14).

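### The follow-up TRIG appears to serve both as a primary outcome and as the control arms' gate to post-trial ayahuasca, a risk of bias favouring A-MR at T4 that the plan does not acknowledge

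*Protocol article*

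**What the plan says.** Section 2.3 (Procedure) of the protocol article states that "participants in either control group (MR or NT) have the option to participate in two ayahuasca sessions over a single weekend", and sets the condition: "once follow-up assessment is completed, if their grief symptom severity are still significant (TRIG ≥ 40" or above). The experimental arm gets its exposure earlier: "Only those in the A-MR group will participate in up to two onsite ayahuasca sessions throughout the therapeutic process". No later benefit is tied to an A-MR participant's score.

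The abstract gives the timing of both grief scales as "administered at baseline, post-treatment, and 3-month follow up". On their status it is explicit: "The primary outcomes will be normal and pathological grief severity as measured by the TRIG and Traumatic Grief Inventory Self-Report (TGI-SR"). Section 2.5.1.1 says of the TRIG: "This self-report measure quantifies the severity of normal grief". Hypothesis 1 (section 2.1) expects A-MR to improve more "compared to both control groups (MR and NT), at post-treatment and 3 months follow-up". In Table 1 the TRIG is marked at enrolment, T0, T3 and T4, and nowhere after T4. Entry to the trial used the same cut-off of 40 (section 2.2).

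**The concern.** On the natural reading, a control participant who fills in the TRIG at T4 supplies a primary outcome value and, with the same answers, settles whether ayahuasca will be offered. An A-MR participant filling in the same form has nothing to gain from either a high or a low score.

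There is reason to think the offer matters to these participants. The Discussion concedes that "the self-referral process relies on the social media presence of psychedelic research and education institutions and associations". It treats this as a limit on generalisability only. The limitations name sequential allocation and self-referral but not this incentive, which bears on internal validity.

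At stake are the two T4 TRIG contrasts, A-MR against MR and A-MR against NT. Any response to the incentive raises control scores, so it makes A-MR look better. A larger sample would not cancel it, and baseline covariates in the mixed model would not adjust for it, because it arises at T4.

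**Working it through.** **Does one score play both roles?** Four statements in the protocol article, side by side:

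- Access rule (2.3): TRIG of 40 or more once follow-up is complete, MR and NT only.
- Outcome (abstract; 2.5.1): TRIG, self-reported, primary.
- Hypothesis (2.1): tested at T3 and at T4 against both control arms.
- Schedule (Table 1): T4 is the last TRIG shown.

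The double use follows by inference. The article does not say that the T4 form supplies the gating score, but it describes no other.

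**How large could the effect be?** The plan gives no figure for over-reporting, so there is nothing of its own to reproduce. What follows is illustrative.

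Inputs from section 2.4: target difference 9.4 TRIG points, d = 0.84, 69 participants in total.

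- Implied SD = 9.4 / 0.84 = 11.19.
- Per arm = 69 / 3 = 23.

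Assumptions, not in the document: T4 scores are roughly normal with SD 11.19, rounded and limited to 13–65; the T4 mean is between 35 and 43; the arms do not truly differ; a control who responds to the incentive reports exactly 40.

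Formula: rise in control mean = q × Σ P(score = k) × (40 − k), summed over the true scores k below 40 from which people respond. Here q is the share of those people who do so.

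*Narrow case: only true scores of 35 to 39 respond.* If all of them do (q = 1):

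| T4 mean | Share at 35–39 | Rise in control mean |
|---|---|---|
| 35 | 17.4% | 0.53 |
| 38 | 17.6% | 0.53 |
| 40 | 17.1% | 0.50 |
| 43 | 15.3% | 0.45 |

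About 0.5 points is therefore the ceiling for this case. With q from 10% to 50% the rise is 0.04 to 0.27 points.

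*Wide case: any control truly below 40 may respond.* The last column is the simulated chance of a false significant result favouring A-MR, for a two-sided 5% t-test at T4 with 23 per arm. Its nominal value is 2.5%.

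| q | Rise in control mean | As % of 9.4 | False result favouring A-MR |
|---|---|---|---|
| 10% | 0.3–0.7 | 3–8% | 3–4% |
| 25% | 0.8–1.8 | 8–20% | 4–9% |
| 50% | 1.6–3.7 | 17–39% | 7–23% |

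In the narrow case, with q up to 50%, that chance stays at about 2.4% to 3.1%, close to nominal.

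The 9.4 points serve only as a yardstick. Section 2.4 defines them for A-MR against NT at post-treatment, not at T4.

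**The case against.** The strongest reply is that the link is inferred. The rule places the offer after follow-up and does not say which TRIG is used. Table 1 covers the study period only: it also omits the controls' later preparation, ayahuasca and integration sessions, so a separate eligibility TRIG could be missing for the same reason. How post-trial eligibility is checked is the sort of detail a condensed article leaves to the full protocol. This stands, and is why the point says *appears*. If a separate assessment exists, one sentence settles the matter.

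Second, the incentive works only if participants know of the condition. The article does not say they are told. It says only that a pre-consent interview covers what taking part involves. This also stands. Knowing the exact number is not needed, however: awareness that access depends on continuing severity would be enough.

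Third, the reach is limited. The TGI-SR, the other primary outcome, gates nothing. T3 is not gated either, and T3 is where the sample size is set. Controls already at 40 or more need not raise their score to qualify.

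A reader might go further and infer that control scores at T4 will be inflated, that every T4 result is compromised, or that the data could reveal nothing about it. The documents support none of these. No over-reporting is shown and only the TRIG is gated. Heaping at 40 among controls, T3-to-T4 change by arm, and divergence of TRIG from TGI-SR could all be examined, although they might not permit a correction.

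**Conclusion.** The point holds as a risk of bias, not as a demonstrated error. It rests on two things the article does not state: that the T4 questionnaire supplies the gating score, and that control participants know access depends on continued severity. Given both, the direction is fixed: control TRIG at T4 can only be raised, which favours A-MR in both T4 TRIG contrasts.

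The size is unknown and may be negligible. It would matter for inference only if a sizeable share of controls well below the cut-off over-reported. The sample size is unaffected. The point deserves attention because the exposure falls on one side only, is not mentioned among the limitations, and is cheap to reduce before data are collected.

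**What to change.** State which TRIG administration determines eligibility for the post-trial offer. If it is T4, separate the two uses:

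1. Have the T4 questionnaire completed and locked before eligibility for the offer is considered.
2. Determine eligibility from a separate, later TRIG administration, leaving the existing cut-off and the offer as they are.
3. Tell participants at consent that their T3 and T4 answers do not determine access.
4. List any remaining incentive as a limitation of the T4 TRIG comparison.

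The cost is one additional 13-item online form for controls who want the offer, and a sentence in the consent material. The separation is not perfect: someone who expects a second TRIG may keep the two sets of answers consistent, so some incentive can remain at T4. Hence the fourth step.
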